#### Hypothesis

The following hypotheses will be tested:Early intervention strategies utilizing physical therapy will result in greater improvements in function and disability in the long-term compared to a stepped usual care approach.Early intervention strategies utilizing physical therapy will result in decreased use of other medical resources (medications, imaging, additional healthcare) in the long-term (1 year) compared to a stepped usual care approach.Baseline psychosocial factors will be associated with changes in clinical outcomes within each treatment group.

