### Data analysis

The data analysis for hypothesis number 1 will use separate analyses of covariance (ANCOVA) to compare the mean change in the primary (OSW) and secondary (NPRS, FABQ, PCS and GRC) outcomes from baseline to each follow-up assessment between groups while controlling for the baseline level of the outcome being analyzed to account for regression to the mean. We will assess the influence of baseline psychosocial measures (PCS and FABQ) on outcomes in both groups by introducing the scores as covariates into the ANCOVA in order to address hypothesis #3. For hypothesis #2, we will use chi-square tests and calculate odds ratios with confidence intervals for the specific healthcare utilization frequently sought by patients with LBP (MRI, injections, work loss as measured by the DA3329 limited duty profile).

We will make every effort to achieve complete data collection. For data that are missing, we will use multiple imputation (MI). Under the MI approach, baseline and follow-up factors beyond the variable being analyzed can be incorporated into the imputation model to account for dependence of the missing data mechanism on other measured factors, such as predictors of patient characteristics and prior scores. We will apply the method of data augmentation using Markov Chain Monte Carlo (MCMC) to generate imputed values. Four steps are involved: a) preparing the dataset for MI, which includes identifying all outcome variables likely to be involved in later planned or unplanned analyses, as well as likely predictors of missingness itself, evaluating distributions for normality and outliers and taking appropriate transformations to normality as needed; b) carrying out the MI, where variance and covariance estimates based on observed data are used to iteratively estimate maximum likelihood values for all participants, with multiple replacement values for each missing data point then being drawn randomly from the posterior distribution and perturbed with error; c) carrying out analyses identically on all versions of the imputed data; and d) combining tests and parameter estimates and adjusting for between-imputation variance to yield the final statistical results.

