### Sample size estimation

Back pain and lower extremity injuries make up 44 % of all injuries for which soldiers seek care. Patients with back pain are seen on a daily basis in this healthcare system. Assuming at least 85 % of the patients complete the OSW at 12 weeks, enrollment of 110 subjects per group (total sample size 220 subjects) will provide at least 84 % power to detect a difference of seven points change in OSW at 12 weeks, assuming a standard deviation in the change in OSW of 16 points (treatment effect = 43.8 % of one standard deviation). The MCID for the OSW has been estimated at 6 points [19]. Previous work with patients with acute LBP indicate that these estimates of anticipated effect size and standard deviation are realistic, [44–46] and would be consistent with detecting an effect that is at least slightly in excess of the threshold for seeing significant change.

The natural history of recovery from back pain and our experience in prior studies suggest that differences tend to become less pronounced at 1 year than at 12 weeks. We believe 12 weeks is the appropriate time frame for the primary endpoint because it reflects the potential impact of treatment, and clinically, if patients are not experiencing improvement at this time point, they seek additional treatments. Thus, we are using this endpoint for the purposes of our power analysis rather than 1 year. The 4-week assessment will allow us to evaluate immediate post-treatment changes, and the 1-year assessment permits us to evaluate the potential long-term effects.

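### Hypothesis 3 asks for an association in each arm, but the planned ANCOVA covariate gives one pooled slope and relies on an equal-slopes assumption that is neither stated nor checked

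*Protocol article*

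**What the plan says.** The protocol article, under Hypothesis, gives the third hypothesis as "Baseline psychosocial factors will be associated with changes in clinical outcomes within each treatment group". The target is therefore an association in usual care (UC) and an association in physical therapy (PT).

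The Data analysis section first sets out the base model: "separate analyses of covariance (ANCOVA) to compare the mean change in the primary (OSW) and secondary (NPRS, FABQ, PCS and GRC) outcomes". One such model is fitted for every follow-up, and its baseline adjustment is described as made "while controlling for the baseline level of the outcome being analyzed to account for regression to the mean". The section then says that the influence of baseline PCS and FABQ will be assessed "on outcomes in both groups by introducing the scores as covariates into the ANCOVA in order to address hypothesis #3". The article names no group-by-score term, no separate fit for each arm and no check that the slopes are alike.

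**The concern.** The hypothesis calls for two slopes and the named method returns one. If the scores predict outcome more strongly in one arm than in the other, the single coefficient understates one association and overstates the other. The report could then say that hypothesis 3 is supported in both arms when it holds in only one.

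Unequal slopes are not far-fetched, because the arms differ by design in the first 4 weeks: PT patients receive up to eight sessions in addition to the care given to both groups. Whether the scores relate to outcome in each arm is the question that hypothesis 3 poses.

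**Working it through.** **Inputs from the protocol (Sample size estimation).** 110 per group; "Assuming at least 85 % of the patients complete the OSW at 12 weeks"; a difference of 7 points; "assuming a standard deviation in the change in OSW of 16 points".

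**Assumptions.** Two-sided alpha of 0.05 (the article states none). Score scaled to SD 1, with the same spread in both arms. Residual SD of 16 OSW points, or 1 in standardised units. The slopes below are illustrative, because the documents give none.

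**The plan's own figure first.** Completers per arm: 0.85 × 110 = 93.5, taken as 93. Standard error of the difference: 16 × √(2/93) = 2.346. Then 7 / 2.346 = 2.983, and power = Φ(2.983 − 1.960) = Φ(1.023) ≈ 84.7% (84.3% by the noncentral t). This reproduces the stated "at least 84%" in substance, so 93 per arm and two-sided 0.05 are a fair basis for the rest.

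**What the covariate estimates.** The planned model is change = a + b·group + c·baseline + d·score. With equal arm sizes and equal score spread, the expected value of d is (slope in UC + slope in PT) / 2. Each arm is misstated by half the difference between the slopes.

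**Standard errors, standardised.**
- Pooled slope: 1/√186 = 0.073
- Slope in one arm: 1/√93 = 0.104, which is √2 ≈ 1.4 times the pooled value
- Difference between slopes: √(2/93) = 0.147

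**Slopes 0.3 (UC) and 0 (PT).** Pooled slope = (0.3 + 0)/2 = 0.15. Then 0.15 / 0.0733 = 2.05, and the chance of significance is Φ(2.05 − 1.96) ≈ 53%. Two simulations of 3,000 trials each gave 51.5% and 51.1%. The interaction test has about the same power, since 0.3 / 0.1466 = 2.05; the simulations gave 51.7% and 52.7%.

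**In OSW points per SD of score (2,000 simulated trials each).**

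| True UC / PT | Plain covariate: mean (significant) | Interaction model: UC, PT |
|---|---|---|
| 4 / 4 | 4.0 (92%) | 4.0, 4.0 |
| 6 / 2 | 4.0 (91%) | 6.0, 2.0 |
| 6 / 0 | 3.1 (72%) | 6.1, 0.1 |

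In the 6 / 0 case the arm-specific test is significant in 94.6% of trials for UC and 5.2% for PT. Treating the two as near-independent, both are significant in about 0.946 × 0.052 ≈ 5% of trials, against 72% for the pooled coefficient.

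**Slope detectable with 80% power.** With 1.960 + 0.842 = 2.802:
- Common slope: 2.802 × 16/√186 = 3.3 points
- One arm: 2.802 × 16/√93 = 4.6 points
- Difference between arms: 2.802 × 16 × √(2/93) = 6.6 points

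**The case against.** A reader might infer that the planned model cannot answer hypothesis 3 at all. The documents do not support that. With group in the model, the coefficient is a within-group slope, not one distorted by the difference between arms. If the slopes are equal it is right for both arms, and more precise than separate slopes (the 4 / 4 row). The defect is that equality is relied on without being stated or checked.

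A reader might also picture slopes of opposite sign, which would cancel: at +0.3 and −0.3 the pooled slope is 0 and is significant in only about 6% of simulated trials. Nothing in the protocol suggests this. Its descriptions of the FABQ and PCS link both constructs to chronic back pain in one direction. Nor does hypothesis 3 claim that the slopes differ, so power for an interaction is not the measure of whether it is answered.

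Finally, the article is condensed, and its reference to both groups could be shorthand for fits by arm set out in a fuller document. That tempers the point but does not remove it: the article ties a specific method to hypothesis 3 by number, and that method as written has one slope.

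**Conclusion.** The mismatch stands in limited form. The hypothesis is stated arm by arm; the method gives one pooled within-group slope, valid for each arm only under an unstated and unchecked equal-slopes assumption. Its size depends entirely on how unequal the slopes are. There is no error if they are equal; under the assumed 0.3 and 0, the UC slope is halved and an absent PT association is reported as present in about half of trials. These slopes are illustrations, not predictions for this trial.

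The severity is moderate. Hypothesis 3 is not the primary comparison and plays no part in the power calculation. The OSW treatment comparison and the sample size are unaffected.

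**What to change.** For hypothesis 3, fit the ANCOVA for OSW at 12 weeks with a group-by-score term, or fit it by arm, separately for PCS, FABQ work and FABQ physical activity. Do likewise for the other clinical outcomes and follow-ups. Report each arm's slope with its 95% CI as the answer to hypothesis 3, and give the interaction estimate as supporting information only.

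Match the multiple imputation to this model: impute by arm, or include the product terms. Otherwise imputed values that follow one common slope will draw the arm-specific slopes together.

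The alternative is to keep the planned model and reword hypothesis 3 as an overall association adjusted for group. Either change is best made before outcome data are examined.

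The cost is a few sentences and some extra model terms, with no new data. The price is precision: the standard error of each arm's slope is about 1.4 times the pooled one, and the interaction test has limited power (about 53% for a slope difference of 0.3).

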**Methods/Design:**

This trial will be a two-arm pragmatic randomized clinical trial occurring at two different clinical sites in the Military Health System. We will assess outcomes and related downstream costs for patients who access physical therapy at the primary care level compared to those that receive usual care only. There will be 220 consecutive patients randomized to receive care in either group (early physical therapy or usual care only) for the first 4 weeks, and these patients will then be allowed to receive any additional care dictated by their primary care provider for the following year. The primary outcome measure is the Oswestry Disability Index. Secondary outcome measures are the Global Rating of Change, Patient Satisfaction and 1-year healthcare utilization. Follow-ups will occur at 4 weeks, 3 months and 1 year.

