### Profile data

A profile is the official instrument used to restrict physical activities and work duties due to medical conditions. It is the only official document that allows a soldier to miss work or training. It provides a list of the activities that cannot be performed along with a duration of time that the restriction is in effect. It is what will be used to track work-loss days. This is recorded in number of days.

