### Healthcare utilization

Finally, healthcare utilization data will be collected from the Military Health System Data Repository (MDR) database and will be confirmed via electronic medical record review. Healthcare utilization data will be used to determine any subsequent medical utilization related to low back pain and the economic impact of those injuries. These data will also allow a comparison of costs between the two treatment approaches used in this study.

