It is feasible for patients with a new episode of LBP to receive physical therapy as part of an early management strategy [8]. However, physical therapy also contributes substantially to the healthcare costs associated with managing LBP [48, 49]. Along with the increasing utilization of physical therapy for LBP, are the corresponding costs that are also increasing [9, 10]. In the last 10 years, physical therapists in the US Army are now providing medical care further up on the front lines with the infantry soldiers as an organic asset to their unit. These therapists are in a prime position to facilitate early access to physical therapy interventions and have done so successfully in a combat-deployed setting [50, 51]. Considering that about 60 % of patients report recurrent symptoms, and 20 % report persistent disabling symptoms following an initial LBP episode [52, 53], research examining the most effective initial management strategies and the potential role of physical therapy is clearly needed. Suboptimal effectiveness of primary care management for patients with an acute episode of LBP can also lead to use of increasingly invasive and costly interventions, including injections, narcotic pain medications and surgical procedures [54–56]. In addition to the significant fourfold increase in prescription pain medication use in soldiers, other significant military healthcare costs are associated with the diagnostic management of these soldiers. In the current combat environment, advanced diagnostic imaging is not readily available [51]. Tests that would routinely be ordered in regular hospitals/clinics, when ordered in a combat setting, often require an evacuation out of the theater, incurring significant additional evacuation costs and time loss from duty. Especially for low back pain, many of these tests do not offer a valid prognosis or provide guidance for treatment and likely lead to an increase in overall medical costs [20, 57]. Reducing trends toward increased utilization and costs associated with prolonged episodes of LBP will require more effective early management strategies [58]. In a combat deployed setting, effective management strategies have the potential to decrease significantly the number of unnecessary evacuations out of the combat theater. The initial primary care encounter may therefore provide the best window of opportunity to improve outcomes and reduce costs related to low back pain.

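### Work loss is recorded in days but assigned a chi-square test, and the hypothesis 2 analysis list leaves out medications, which the hypothesis names

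*Protocol article*

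**What the plan says.** Hypothesis 2 (Hypothesis section) predicts "decreased use of other medical resources (medications, imaging, additional healthcare) in the long-term (1 year") under early physical therapy. Its analysis is in one sentence of the Data analysis section: "we will use chi-square tests and calculate odds ratios with confidence intervals for the specific healthcare utilization frequently sought by patients with LBP". The items follow in brackets: "MRI, injections, work loss as measured by the DA3329 limited duty profile". No wording marks them as examples.

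The Profile data section describes the duty-limitation profile as the source for work loss: "It is what will be used to track work-loss days", and "This is recorded in number of days". The Data collection section lists lost work or training time among the secondary outcomes.

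The Treatment procedures section offers every subject, before randomization, an optional activity excusal or modification of up to 30 days and an optional 10-day prescription of NSAIDs and/or muscle relaxers.

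The only other between-group method stated is ANCOVA, for the Oswestry score, pain rating, fear-avoidance, catastrophizing and global rating of change.

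**The concern.** An odds ratio from a chi-square table compares two categories. Work loss is collected as a number of days, so the stated method requires the days to be cut into categories, and the article gives no cut-point. The natural reading is any loss against none. On that reading, a soldier with 3 restricted days and one with 90 count the same. If early physical therapy shortened restrictions without changing who receives one, the planned test would see nothing.

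The baseline excusal adds to this. If it counts as work loss, having any profile may be common in both arms because of an offer made before allocation.

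Medications are a separate mismatch. They are the first resource named in hypothesis 2, yet they are not in the list of items analysed for it, and the ANCOVA list does not take them up.

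At stake is the conclusion on a named hypothesis and a secondary outcome. The primary endpoint, the Oswestry score at 12 weeks, is not affected.

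**Working it through.** **The plan's own figure.** The only stated power concerns the Oswestry score. Inputs from Sample size estimation: 110 per arm, 85% completion, difference 7, SD 16; two-sided 5% is assumed. Completers per arm = 110 × 0.85 = 93.5. z = 7 / (16 × √(2/93.5)) = 7/2.340 = 2.99; power = Φ(2.99 − 1.96) ≈ 85%. The stated figure of at least 84% reproduces. No power is given for hypothesis 2, and no distribution of work-loss days, so everything below is illustration on assumed inputs.

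**Case A: mean days differ.** Assume 110 per arm, no dropout, negative binomial days with means 20 v 12, variance μ + μ²/k, and k from 0.3 to 1.0.

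- Share with any loss: p = 1 − (k/(k+μ))^k. At k = 0.5: 1 − (0.5/20.5)^0.5 = 84.4% and 1 − (0.5/12.5)^0.5 = 80.0%.
- Chi-square on any/none: SE = √[(0.844 × 0.156 + 0.80 × 0.20)/110] = 0.0515; z = 0.0438/0.0515 = 0.85; two-sided power ≈ 14%.
- Rate ratio with known k: SE of the log ratio = √[(1/20 + 1/12 + 2/k)/110] = √(4.133/110) = 0.194; z = ln(20/12)/0.194 = 0.511/0.194 = 2.64; power = Φ(0.68) ≈ 75%.

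The rank-test column is simulated; the other columns use the formulas above.

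| k | any loss, 20 v 12 days | chi-square | rank test | rate ratio |
|---|---|---|---|---|
| 0.3 | 72% v 67% | 11% | about 30% | 54% |
| 0.5 | 84% v 80% | 14% | about 53% | 75% |
| 1.0 | 95% v 92% | 15% | about 88% | 96% |

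Simulation of all three tests gives 11-14%, 30-88% and 55-95%, which agrees within simulation error. The rate-ratio figures are somewhat optimistic because the dispersion is treated as known. The rank test needs no such value.

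**Case B: only duration differs.** Same share with any loss in both arms; days among those with loss are 1 plus a gamma-Poisson count (shape 1) of mean 30 v 15. Over 3,000 simulated trials per setting:

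| share with any loss | chi-square | rank test |
|---|---|---|
| 50% | 5% | 20% |
| 70% | 5% | 55% |
| 90% | 5% | 93% |

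Chi-square stays at its false-positive rate.

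**Case C: share and duration both fall.** With gamma-Poisson means 30 v 20: at 70% v 60% with any loss, chi-square 36% and rank test 67%; at 90% v 85%, 21% and 73%.

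**Case D: only the share differs.** With 50% v 35% and the same duration, chi-square 61% and rank test 57%. Here the stated test is slightly better.

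**Medications.** No arithmetic applies. Hypothesis 2 names medications, imaging and additional healthcare. In the analysis list, MRI represents imaging and injections are one form of additional healthcare. Nothing represents medications.

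**The case against.** The strongest defence is that decreased use can fairly mean fewer users, for which chi-square and odds ratios are suitable. That stands for MRI and injections. It does not stand for work loss, which the article itself says is tracked in days.

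The article also never says any/none; a threshold in days is possible. That is correct, and Case B would then not apply exactly. But no threshold is given, and any single cut registers only subjects who move across it.

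The power figures rest on assumed means and on data drawn from the same model that the rate ratio uses. Excusals of up to 30 days could also clump the durations. This is fair: the figures show direction and possible size, not the trial's actual power, and Case D goes the other way.

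A reader might infer several stronger points that the documents do not support:

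- *That the trial cannot conclude on costs.* The abstract says "We will assess outcomes and related downstream costs for patients", and the Healthcare utilization section says "These data will also allow a comparison of costs between the two treatment approaches used in this study". Chi-square cannot serve that comparison, but the article does not assign it to costs, and a method may sit in an analysis plan not shown.
- *That protocol physical therapy sessions would be left out of the costs.* The Discussion notes that "physical therapy also contributes substantially to the healthcare costs associated with managing LBP", but nothing in the article limits the comparison so as to exclude those sessions.
- *That nearly everyone will have a profile.* The excusal is optional and no uptake is given, so a ceiling is a risk only.
- *That all care beyond imaging is missing from the list.* Injections are on it; only medications are plainly absent.

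**Conclusion.** The point holds on two matters of stated text. A categorical test is fixed for work loss, an outcome recorded in days, so duration is lost. Medications are named in hypothesis 2 but absent from its analysis list.

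Under the assumed inputs, the loss from categorising ranges from large (11-14% power against 30-88% for a rank test when mean days differ) through total (5% when only duration differs) to a slight advantage for chi-square (61% v 57% when only the share differs). The conclusion assumes that chi-square with odds ratios means a two-category split, most naturally any against none. The change should be made, but it concerns secondary outcomes and does not touch the sample size or the primary analysis.

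**What to change.** In the Data analysis section:

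- Compare work-loss days over 1 year as a quantity, for example by negative binomial regression or a mean difference with a bootstrap confidence interval, with a rank test as a check.
- Keep chi-square tests and odds ratios for MRI and injections. The share with any work loss can be reported beside the days.
- Add medication use as a hypothesis 2 endpoint, with its definition and test.
- State whether the excusal and the prescription offered at baseline are counted.

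The cost is analysis wording and a little programming. Profile days are already collected, and medication use should be obtainable from the utilization data (an assumption, since the article does not list the fields). The downside is that days need a method suited to skewed and possibly clumped data, which takes more care to fit and explain than a two-by-two table.
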